**Fig. 1 Fig1:**
[figure not shown]
Flow chart of the study. The safety assessment contains a routine blood test, kidney function test, and liver function test. *BCQ* Body Constitution Questionnaire, *CHM* Chinese herbal medicine, *CTCAE* Common Terminology Criteria for Adverse Events (version 4), *ECOG* Eastern Cooperative Oncology Group (score), *FACT-B* Functional Assessment of Cancer Therapy - Breast Cancer, *MEAD* Meridian Energy Analysis Device, *TCM* traditional Chinese medicine

A participant will be discontinued from the study if she withdraws from chemotherapy, if a severe adverse event (AE) occurs, or if the researchers, for any safety reason, judge the participant’s continuation in the study to be inappropriate.

### Inclusion criteria

Subjects are eligible to participate if they are female and meet the following criteria: (1) age > 20 years; (2) histologically proven stage 1–3 breast cancer after surgery; (3) duration from the end of radical surgery to the beginning of the trial of less than 1 month; (4) Eastern Cooperative Oncology Group (ECOG) Performance score of 0–2 points; (5) agreement to participate in this study and sign informed consent.

### Exclusion criteria

Subjects will be excluded if they meet any of the following criteria: (1) comorbidity of inadequate heart, liver, kidney, or hematopoietic function or other serious diseases; (2) pregnancy or lactation; (3) history of mental illness; (4) distant metastasis and/or expected lifetime of less than 3 months; (5) have accepted external TCM intervention such as acupuncture, moxibustion, cupping, etc.; (6) treatment with other medicinal herbs outside our hospital.

### Outcome measurements

One investigator will be responsible for the follow-up of each participant at baseline and every 3 to 6 months. The schedule for data collection and follow-up by telephone or outpatient visits is shown in Table 2.

**Table 2 Tab2:** Trial schedule of enrollment, interventions, and data assessments

Time point	Screening	Period of adjuvant chemotherapy			Follow-up, months			
	−4–0 week	1	3	6	9	12	…	36
Enrollment								
Informed consent	X							
Eligibility screen	X							
General assessment								
Demographic data	X							
Medical history	X							
Treatment situation	X							
TCM program								
CHM intervention		X	X	X				
TCM cohort only	X	X	X	X	X	X	X	X
Assessment								
FACT-B	X		X	X				
ECOG	X		X	X				
BCQ	X			X				
MEAD	X			X				
Imaging examination (CT, type B ultrasonography, bone scan)	X		X	X	X	X	X	X
Tumor markers (CEA & CA15-3)	X		X	X	X	X	X	X
Safety indicators	X	X	X	X	X	X	X	X
Chemotherapy-induced side effect, CTCAE		X	X	X	X	X	X	X
Cohort migration					X	X	X	X
Combined medication					X			

*ECOG* Eastern Cooperative Oncology Group, *FACT-B* Functional Assessment of Cancer Therapy-B, *BCQ* Body Constitution Questionnaire, *MEAD* Meridian Energy Analysis Device, *CT* Computed tomography, *CEA* Carcinoembryonic antigen, *CA15-3* Cancer antigen 15-3, *CTCAE* Common Terminology Criteria for Adverse Events, *CHM* Chinese herbal medicine, *TCM* Traditional Chinese medicine

### Primary outcome

The primary outcome of this study is 3-year DFS, defined as the period after curative treatment when no disease can be detected. This indicator will be calculated at the end of the study. The outcome assessment with regard to survival, local and regional relapse, and distant metastasis will be obtained by either review of the hospital records system or contact by mail or phone. The date of last evaluation will be recorded if patients have neither recurrence nor metastasis unless they reach censored data or there is loss of follow-up.


### Safety assessments

In addition to the focus on prognosis and QOL, TCM pattern, meridian energy, and chemotherapy-related side effects of breast cancer patients with CHM, the safety of the CHMs taken during the period of adjuvant chemotherapy is also a major focus. Routine blood tests and liver and kidney function tests are registered at baseline, and the occurrence of any functional damage after taking CHM is evaluated at each follow-up visit. Moreover, tumor markers (carcinoembryonic antigen [CEA] and cancer antigen [CA15-3]) and routine image examinations (computed tomography and breast ultrasonography) are recorded to estimate whether an increased chance for tumor progression occurs in the CHM group. In addition, based on the CTCAE issued by the National Cancer Institute (NCI), all AEs including toxicity and side effects must be reported throughout the course of the study. In case of any serious AE occurring, experimental intervention should be ceased immediately and proper treatments must be provided. At the same time, the severity of the AE and the relationship with CHM should be evaluated.

### Sample size calculation

The primary objective of the research is the 3-year DFS rate, which we used as the basis for the calculation of sample size. According to a relevant large-scale cohort study [21], the 3-year DFS rate of patients with early breast cancer after surgery is about 85%, and we expect it to increase to 95% with CHM treatment. The sample size for differences between two independent proportions was calculated by a G-Power (V.3.1) formula to ensure 80% power using a two-sided test with a significance level of α = 0.05. We need 141 participants in each cohort. Considering a projected dropout rate of 10%, the sample size of each cohort should be 155 and the total sample size should be 310.

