**Methods/design:**

This is a non-randomized, single center, prospective cohort study begun in November 2018 in Kaohsiung, Taiwan. A sample of 310 participants diagnosed with early breast cancer was recruited from the Breast Cancer Research Team and will be followed up every 3 to 6 months until October 2023. Detailed information of the participants, including general information, history of cancer, quality of life, side effects and safety of treatment, TCM body constitution, and meridian energy analysis, was collected face to face at baseline.

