## Methods/design

### Study design

This study is a non-randomized, single center, prospective cohort study. The study began in November 2018 and is currently ongoing. A cohort of 310 patients aged more than 20 years with breast cancer with histologically diagnosed stages 1–3 after partial or radical surgery were enrolled from an academic medical center. All participants will complete six to eight cycles of adjuvant chemotherapy, which may last 6 months. The standard chemotherapy regimens include anthracycline-, taxane-, or anthracycline plus taxane-based chemotherapy specified by the NCCN guidelines, based on their disease states. At the time the participants enter the study, the time between surgery and initial chemotherapy is not more than 1 month. The study consists of two stages. Stage I is a cross-sectional study at baseline, and stage II is a cohort study across 3 years of follow-up. Participants will be followed up every 3 to 6 months for 3 years, until recurrence or death. The feasibility and precision of the entire process will be overseen by two supervisors. To ensure that patients adhere to the follow-up schedule, we remind patients of their scheduled visits by telephone or text message. Additionally, incentives are used to express appreciation for the participants’ recruitment and retention throughout the years.

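### Minor arithmetic slip: 155 per cohort less the projected 10% dropout leaves about 139.5, just under the 141 that the protocol says it needs

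*Protocol article*

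**What the plan says.** The Sample size calculation section bases the trial on the 3-year disease-free survival (DFS) rate. It assumes that "the 3-year DFS rate of patients with early breast cancer after surgery is about 85" per cent and adds that "we expect it to increase to 95% with CHM treatment". On the method it says: "The sample size for differences between two independent proportions was calculated by a G-Power (V.3.1) formula", and the aim is "to ensure 80% power using a two-sided test with a significance level of α = 0.05". The result is "We need 141 participants in each cohort".

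The section then allows for 10% dropout and states that "the sample size of each cohort should be 155 and the total sample size should be 310". It does not print the formula that leads from 141 to 155.

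The total is repeated in the Abstract ("A sample of 310 participants") and under Study design ("A cohort of 310 patients"). These agree with the sample size section. They are not further errors, only places where a changed figure would have to be carried through.

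**The concern.** An allowance for dropout should leave the required number once the expected losses have occurred. Dropout is ordinarily a fraction of those enrolled, so the required number is divided by one minus the dropout rate. Multiplying by one plus the rate always gives too few, though only slightly when the rate is small.

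Here the requirement, the dropout rate and the enrolment target stand together in one paragraph and do not agree. No missing analysis plan or fuller protocol is needed to see this. What is at stake is a stated figure that misses its own requirement, not the validity of the study.

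**Working it through.** **Inputs**, all from the Sample size calculation section: 3-year DFS 0.85 and 0.95, two-sided α = 0.05 (z = 1.960), power 80% (z = 0.842), 141 per cohort before dropout, 10% dropout, 155 per cohort and 310 in total after dropout.

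**1. Reproduce 141.** Pooled two-proportion formula without continuity correction, with mean proportion 0.90:

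- n = [1.960 × √(2 × 0.90 × 0.10) + 0.842 × √(0.85 × 0.15 + 0.95 × 0.05)]² / 0.10²
- = [1.960 × √0.18 + 0.842 × √0.175]² / 0.01
- = 140.1, rounded up to **141**.

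This matches the protocol. Other common variants do not: unpooled 138, arcsine 133, continuity-corrected 160. The base calculation is sound.

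**2. Apply the protocol's own dropout to its own target.**

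- 155 × 0.90 = **139.5** per cohort, against 141.
- 310 × 0.90 = **279** in total, against 2 × 141 = 282.

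**3. Find the number that retains 141.**

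- 141 / 0.90 = 156.7, so **157** per cohort and **314** in total.
- Check: 157 × 0.90 = 141.3, which is at least 141.

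**4. How 155 may have arisen.**

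- 141 × 1.10 = 155.1, rounded down to 155.
- From the unrounded value, 140.1 × 1.10 = 154.1, rounded up to 155.
- Division does not give 155 from either start: 141 / 0.90 rounds up to 157, and 140.1 / 0.90 = 155.7 rounds up to 156.

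Multiplication by 1.10 is therefore the likely route, but this is inferred. Step 2 holds however 155 was obtained.

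**5. Dropout that 155 can absorb.** 1 − 141/155 = 0.090, so **9.0%**.

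**6. Power under the sizing formula, with dropouts removed altogether.** Power = Φ{[0.10 × √n − 1.960 × √0.18] / √0.175}:

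| n per cohort | Power |
|---|---|
| 139 | 79.7% |
| 139.5 | 79.8% |
| 141 | 80.25% |

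The loss is about 0.5 percentage points.

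**7. The planned DFS test.** The Statistical analysis section compares the cohorts by Kaplan–Meier and log-rank, not by a difference of two proportions. A simulation of the log-rank test (20,000 runs per scenario) needs assumptions that the article does not state: exponential DFS reaching 85% and 95% at 3 years, and dropout times uniform over the 3 years.

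| Scenario | Power |
|---|---|
| 155 per cohort, 10% dropout | about 84% |
| 157 per cohort, 10% dropout | about 84% |
| 139 per cohort, complete follow-up (as if every dropout left at time zero) | about 81% |

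Under these assumptions, 155 and 157 cannot usefully be told apart, and even the extreme case stays above 80%.

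**The case against.** The strongest reply is that nothing of substance turns on this. The gap is 2 patients per cohort. The control rate is itself only approximate and the dropout rate a projection, so the difference between 9.0% and 10% lies well inside the uncertainty of the inputs. Patients choose for themselves whether to take Chinese herbal medicine (Study settings and participants), so the split between cohorts is not under the investigators' control. Propensity score matching is planned (Discussion, limitations). Either could move the analysed numbers by more than 2 per cohort. All of this stands, and it is why the point carries the lowest severity.

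A second reply is that counting 139 per cohort treats each dropout as contributing nothing. The Primary outcome section records the date of last evaluation and refers to censoring and loss to follow-up, and the log-rank test uses the time at risk of censored patients. This also stands. A reader might infer that the trial is underpowered for its DFS comparison. The documents do not support that: 79.7–79.8% belongs to the sizing formula with dropouts excluded, and step 7 shows no fall below 80% under the planned test with the assumptions given there.

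A third reply is that the method of inflation is unknown. That is so. A reader might take it as established that the sponsor multiplied where division was needed, but the article prints no formula. Only the mismatch between 155, 10% and 141 is established.

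None of these replies makes 155 consistent with 141 at 10% dropout of those enrolled.

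**Conclusion.** The point holds as a small arithmetic slip. By the protocol's own figures, 310 patients less 10% leaves 279, which is 3 fewer than the 282 required. After rounding up, the consistent enrolment figure is 314, 4 more than stated.

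This rests on two conventions: dropout counted as a share of those enrolled, and the requirement taken as the printed 141. The first matters most. If 10% were meant as a share of those who complete, 141 × 1.10 = 155.1 would miss by only a fraction of a patient, but that is not the ordinary meaning and the article does not state it.

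The calculation does not show a material loss of power for the primary analysis, and it gives no reason to recruit more patients.

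**What to change.** Change one sentence in the Sample size calculation section, in either of two ways.

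- **Keep 310 (preferred).** State that 155 per cohort retains the required 141 if dropout is at most 9.0%. Equivalently, state that with 10% dropout about 139 per cohort remain, with about 79.7–79.8% power. If the power figure is printed, label it as applying to the two-proportion sizing formula with dropouts excluded, so that it is not read as the power of the log-rank analysis. Recruitment, the Abstract and Study design stay as they are.
- **Print the correctly inflated figures.** Give 157 per cohort and 314 in total, and carry 314 through to the Abstract and Study design if it becomes the enrolment target.

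In both cases, print the inflation formula. The first option costs one sentence and is open even if enrolment is complete. The second costs up to 4 more patients, for no useful gain in power under the planned test.

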### Statistical analysis

All statistical analyses will be performed in SPSS version 17.0 (SPSS Inc., Chicago, IL, USA). Statistical significance will be defined as *P* < 0.05. Based on the data distribution, the measurement data will be analyzed by *t* test or the Mann–Whitney *U* test, and the counting data by the χ^2^ test or Fisher’s exact test. Kaplan–Meier survival analyses will be used with regard to the DFS, and the log-rank test will be used between the two cohort groups. Repeated measures analysis of variance (ANOVA) and linear mixed models will be used to evaluate the repeated measures such as QOL, TCM pattern, and MEAD related to breast cancer and to compare the differences between the two groups. Therapeutic efficiency will be analyzed using the data of the full analysis set (FAS) and per protocol set (PPS); safety evaluation will be based on the data of the safety analysis set (SS) for statistical analysis.

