Increasing numbers of patients use a wide range of complementary and alternative medicine (CAM) therapies, including herbs, vitamins, homeopathic remedies, and Chinese herbal medicines (CHMs), during their anticancer treatment. The use of CHMs based on traditional Chinese medicine (TCM) theory for breast cancer has been recorded in ancient Chinese books for more than 2000 years. In Taiwan, nearly 20% of patients seek CHM as part of the treatment for their breast cancer [8]. As a CAM therapy for breast cancer, CHM has gradually shown its effects in controlling the progression, increasing the susceptibility to radiotherapy and chemotherapy, elevating immunity, and decreasing the toxicities or side effects of cancer therapies [9]. Authors of a systematic review demonstrated that the combined use of CHM with chemotherapy was an appropriate adjunctive therapy for immediate tumor response and chemotherapy-induced toxicities [10], but the supporting evidence was insufficient because most of the randomized controlled trials (RCTs) had poor study design. In addition, it is unproven whether combined CHM therapy is more effective than the standard adjuvant chemotherapy for clinical prognosis, especially in early breast cancer. Therefore, we planned to perform a single center prospective cohort trial to investigate whether the intervention of CHM can improve the prognosis of postoperative breast cancer patients in terms of disease-free survival (DFS), and then to provide evidence that TCM treatment is effective and safe. Meanwhile, this study can provide a breast cancer patient information database, which may correct the guidelines for TCM treatment, build trust between Western medicine doctors and TCM practitioners, and enhance the role of TCM in integrated medical care.

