### Study settings and participants

The study is being performed in Kaohsiung Chang Gung Memorial Hospital (KCGMH) in Taiwan. Approximately 2–4 weeks after the completion of surgery, the early breast cancer patients are hospitalized for port-a-catheter implantation and administration of the first cycle of adjuvant chemotherapy. At that time, we are referred to the patients by the Breast Cancer Research Team on the day of their hospitalization. Participant screening is implemented by our department specialists with a background in oncology. For eligible patients, the researcher provides details on the purpose, specific content, instructions on how to complete the trial, and precautions of cancer treatment. After we obtain their informed consent, patients are enrolled in the study.

During the period of adjuvant chemotherapy, the participants can decide whether to accept the CHM intervention based on their personal conditions and evaluation of their own physiques. If a patient is willing to see TCM practitioners, we arrange CHM treatment for her. However, participants treated with CHM need to receive such treatment for at least half of the whole period. Participants taking CHM during the period of adjuvant chemotherapy are referred to as cohort 1, and patients receiving only chemotherapy without CHM belong to cohort 2. CHM is prescribed by TCM practitioners with more than 5 years of experience according to the TCM Treatment for Breast Cancer protocol developed in our Integrative Cancer Center (Table 1). The protocol and consensus assessment used in the study are based on the integration of empirical data and previous research of TCM syndromes in breast cancer [11, 12]. We record the number of TCM clinic visits, common CHM prescriptions, and days of taking the medicine, but we do not interfere with the treatment of TCM practitioners. The study project and estimated recruitment numbers are presented in Fig. 1.

**Table 1 Tab1:** Syndrome differentiation-based CHM treatments for patients with breast cancer during adjuvant chemotherapy period

Pattern type	Symptoms	Treatment principle	Prescriptions (components)

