Some limitations of this study are as follows. First, the study is an observational study, so the evidence level is lower than that of an RCT. TCM treatments are individualistic and dynamic in approach because they are based on clinical signs and symptoms at different stages, so there may not be a standard treatment for a population [27]. Moreover, the difficulties of randomization and blinding, selection of controls, and patient’s willingness and motivation to complete a study are other issues in conducting an RCT [28]. Although incorporating TCM principles in an RCT poses a challenge, we still can employ an evidence-based model for this traditional practice [29]. Second, baseline characteristics between the two cohorts may be imbalanced if the patients tend to choose combined CHM treatment in stage I. To resolve this problem, we will analyze the data by propensity score matching to control for some possible related factors. Third, the evidence supporting our TCM Treatment for Breast Cancer protocol is not sufficient. The protocol was developed in 2016, and it has not since been popularized due to a lack of large-scale clinical research. This will influence the rationality of treatment using this protocol, and our results may not be representative of the whole population. Finally, queue migration and the long time required for follow-up are both challenges in a cohort study. One way to avoid such problems is to strengthen the role of the cancer case manager in effective follow-up of the participants.

This proposal outlines the methodology for an observational study of adjuvant chemotherapy combined with CHM on the prognosis of patients with early breast cancer; the study adheres to the Standard Protocol Items: Recommendations for Interventional Trials (SPIRIT) statement [30]. The SPIRIT checklist is provided as Additional file 1. Results of this study should help provide support and parameters for the use of integrative TCM and anticancer treatments in patients with breast cancer.

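### The only comparison given for 3-year DFS is an unadjusted log-rank test between self-selected cohorts, and the propensity matching promised in the limitations is neither tied to DFS nor ranked against it

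*Protocol article*

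**What the plan says.** Exposure is the patient's own choice. Under Study settings and participants, "the participants can decide whether to accept the CHM intervention based on their personal conditions and evaluation of their own physiques". The groups follow from that choice: "Participants taking CHM during the period of adjuvant chemotherapy are referred to as cohort 1", and those who have chemotherapy without CHM form cohort 2.

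The section Primary outcome states: "The primary outcome of this study is 3-year DFS". For DFS, the Statistical analysis section gives Kaplan-Meier curves and adds that "the log-rank test will be used between the two cohort groups". Efficacy is to be analysed on the full analysis set and the per protocol set. The section mentions no regression model for DFS, no stratification, no weighting and no matched set.

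Adjustment appears in one place, the second limitation in the Discussion. There the authors accept that the cohorts may differ at baseline if patients lean towards CHM, and say that "we will analyze the data by propensity score matching to control for some possible related factors".

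**The concern.** A log-rank test on the whole of two self-selected cohorts compares the patients as well as the treatments. If whatever leads a patient to choose CHM is also related to recurrence, the test can reject when CHM does nothing, or miss an effect that exists. The authors see this risk, but their remedy sits outside the section that defines the analysis.

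Two things are at stake. First, following Statistical analysis as written gives a DFS comparison with no protection against confounding. Second, the article points to two DFS results, unmatched and matched, and does not say which one carries the conclusion, so that choice could be made after both are known. This matters more because the Background says the study is to "provide evidence that TCM treatment is effective and safe".

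**Working it through.** **1. The plan's own figure.** Inputs from Sample size calculation: 3-year DFS of 85% and 95%, two-sided alpha 0.05, power 80%. With a pooled variance under the null and no continuity correction:

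n = [1.96 × √(2 × 0.90 × 0.10) + 0.8416 × √(0.85 × 0.15 + 0.95 × 0.05)]² / 0.10² = (0.8316 + 0.3521)² / 0.01 ≈ 140.1, rounded up to 141 per cohort.

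This reproduces the stated 141. The stated 155 is 141 × 1.10 = 155.1, and 2 × 155 = 310. The point does not rest on an arithmetic error.

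**2. The sections side by side.**

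| Question | Statistical analysis | Discussion, second limitation |
|---|---|---|
| Method | Kaplan-Meier, log-rank | Propensity score matching |
| Population | Full analysis set and per protocol set | Matched patients |
| Tied to DFS? | Yes | Not stated |
| Which result is the main one? | Not stated | Not stated |
| Reflected in the sample size? | Two independent proportions | No allowance for unmatched patients |

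**3. What an unadjusted test can do. All imbalance values here are assumptions; the document gives none.** Take no CHM effect, 141 per cohort, overall 3-year DFS of 85%, and one binary prognostic factor. Two strengths were used: 3-year DFS of 91% in low-risk and 75% in high-risk patients (high-risk share 37.5%, since 0.625 × 0.91 + 0.375 × 0.75 = 0.85), and 95% against 70% (share 40%, since 0.60 × 0.95 + 0.40 × 0.70 = 0.85). The high-risk share is then shifted so that cohort 1 has fewer high-risk patients. Event times are exponential and censored at 3 years, with 4,000 simulated studies per row and rejection at |z| > 1.96.

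| DFS in strata | Imbalance (points) | DFS cohort 2 / cohort 1 | False gap (points) | Unadjusted log-rank rejects | Stratified log-rank rejects |
|---|---|---|---|---|---|
| 91% / 75% | 0 | 85.0% / 85.0% | 0 | 4.6% | 4.8% |
| | 10 | 84.2% / 85.8% | 1.6 | 6.4% | 4.7% |
| | 20 | 83.4% / 86.6% | 3.2 | 11.9% | 5.4% |
| | 30 | 82.6% / 87.4% | 4.8 | 20.7% | 4.9% |
| 95% / 70% | 0 | 85.0% / 85.0% | 0 | 4.7% | 5.0% |
| | 10 | 83.75% / 86.25% | 2.5 | 8.5% | 4.4% |
| | 20 | 82.5% / 87.5% | 5.0 | 21.7% | 4.8% |
| | 30 | 81.25% / 88.75% | 7.5 | 43.0% | 5.1% |

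Hand check of the last row, treating DFS as a proportion: standard error under the null √(0.85 × 0.15 × 2/141) = 0.0425; standard error at the actual rates √[(0.8125 × 0.1875 + 0.8875 × 0.1125)/141] = 0.0423; rejection Φ[(0.075 − 1.96 × 0.0425)/0.0423] ≈ Φ(−0.20) ≈ 42%, close to the simulated 43%.

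Once the factor is imbalanced, nearly all rejections favour the better-prognosis cohort. Stratifying on the factor keeps the rate at 4.4% to 5.4%. The false gap of 1.6 to 7.5 points compares with the planned difference of 10.

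**4. What matching costs.** Power for 85% against 95% with m patients per matched cohort is Φ{[0.10√m − 1.96√(2 × 0.90 × 0.10)] / √(0.85 × 0.15 + 0.95 × 0.05)}. If 80% of 141 are matched, m = 112.8 and power is Φ[(1.062 − 0.832)/0.418] = Φ(0.55) ≈ 71%. With 90%, 70% and 50% matched it is 76%, 65% and 51%. Keeping 141 matched per cohort at 80% matched and 10% dropout needs 141/(0.9 × 0.8) ≈ 196 per cohort. The matched shares are assumptions.

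**The case against.** The best defence is that adjustment is promised. The limitations say the authors will match, and the two sections are compatible: matching could form the cohorts that the log-rank test then compares. The log-rank test is nowhere called primary, crude or unadjusted. This stands in part. A reader might infer that the protocol fixes a crude log-rank P value as its primary result, or that it plans no adjustment at all. The document supports neither. What remains is that no sentence joins the two sections, and the efficacy sets named are the full and per protocol sets, not a matched one.

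A reader might also infer that the bias favours CHM, or that the error rate in this trial is some particular figure. Neither can be shown. Patients choose "based on their personal conditions and evaluation of their own physiques", which names no prognostic factor. The abstract says patients seek traditional Chinese medicine for relief of symptoms and side effects, which could draw sicker patients and bias against CHM.

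Nor are all the secondary comparisons necessarily crude: linear mixed models can carry covariates, and the section does not say that they will not. The covariate list, caliper, balance checks and sensitivity analyses may sit in an analysis plan that is not shown, so their absence is no fault here. Finally, the abstract already frames the aim as an association and the limitations concede a lower evidence level than a randomized trial, so the Background's stronger wording is not the whole of the authors' position.

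**Conclusion.** The point holds in this form: the section that defines the analysis gives an unadjusted log-rank test as the only comparison for the primary outcome of a study with self-selected exposure, and the promised matching is neither linked to DFS nor ranked against that test. This is more than detail left to an analysis plan, because the article states one analysis in its methods and points to another in its limitations.

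The range of about 6% to 43% is hypothetical. It rests on a single factor of assumed strength, an imbalance of 10 to 30 points, no CHM effect, and the 85% given for patients without CHM reused as the common rate. At the weak end the inflation is slight. The qualitative conclusion needs none of these values: a comparison without adjustment does not guard against confounding, and two unranked results leave room for choice.

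**What to change.** Carry the commitment in the limitations into Statistical analysis:

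- Name one confounder-adjusted DFS analysis as primary. It can be the propensity score matching already promised, or propensity score weighting, which keeps more patients; state the population to which the chosen method applies.
- Base it on prespecified prognostic covariates measured before CHM starts (for example age, stage, ECOG score, type of surgery and planned chemotherapy regimen), and run it whatever imbalance is observed. The full list can go in the analysis plan.
- Label the unadjusted log-rank test descriptive.
- Apply the same adjustment to the secondary between-cohort comparisons.
- Word the conclusion as an association, in line with the abstract, and bring the Background sentence into line with it.
- If matching is kept, restate power for the expected matched number (about 71% if 80% of 141 per cohort are matched), or revise the sample size.

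The cost is protocol wording, modest programming, possibly software beyond SPSS 17, and a somewhat wider interval than the unadjusted one. The change should be made before DFS is compared between the cohorts.
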